### Schedule of assessments

The first study visit will be performed immediately after study participants provide written informed consent, enrolment and randomization. Anthropometric information, baseline treatment and laboratory data will be recorded. Elective cardiac surgery will be programmed within 30 days of the first visit. The research team will provide study medication to each participant. Doses 1–5 of study medication will be administered daily on the last 5 days before surgery (Days –5 to –1). The sixth dose will be administered within the first 8 h after surgery (Day 0). Doses 7–13 will be administered daily during the first 7 days after surgery (Fig. 1). Previous research has not adequately defined the best timing for SGLT2i initiation to prevent ischemia–reperfusion injury with protocols starting SGLT2i administration both before and after the onset of injury [21, 23, 24]. However, empagliflozin has been shown to reach the peak of its glycosuric effect within the first 24 h after its administration, with further stabilization over the next 72 h. Moreover, renal protective effects of SGLT2i seem to appear early after treatment initiation [23, 37]. We chose to start study medication 5 days before surgery to ensure a stable and sustained effect of empagliflozin on the kidney.

The visit schedule is summarized in Fig. 2. Vital signs, blood and urine samples, as well as information about study endpoints, adverse events and other outcomes of interest, will be recorded in each visit.

**Figure 2: fig2:**

Study visit schedule. D, discharge; ICU, intensive care unit; IO, intraoperative; PO, preoperative.

Discontinuation of the study drug will be required for patients who develop any serious adverse event that could reasonably be related to study medication, at the discretion of the treating physician. Patients who prematurely discontinue the study drug but do not withdraw consent will continue follow-up visits as scheduled if possible.

### Outcome definitions and background medication

The primary endpoint of the study will be the time to the first occurrence of any major adverse kidney event during the first 90 days after surgery (MAKE90). The components of MAKE90 will be a ≥25% eGFR decline from preoperative baseline, the start of renal replacement therapy or patient death. Secondary, tertiary and safety endpoints are listed in Table 2. Treating physicians will be responsible for adjudicating possible postoperative complications.

**Table 2: tbl2:** Primary, secondary, tertiary and safety endpoint of the VERTIGO trial.

Primary endpoint
Proportion of patients that present MAKE90, defined as one or more of the following:
- ≥25% eGFR decline from preoperative baseline
- Start of renal replacement therapy
- Patient death
Secondary endpoints
- Proportion of participants who developed any stage of AKI defined according to KDIGO guidelines during index admission
- Proportion of patients who suffered a Stage 3 AKI according to KDIGO guidelines during index admission
- Proportion of patients who required renal replacement therapy during index admission
- Proportion of patients who died during index admission
- Proportion of patients that maintain ≥25% eGFR decline from preoperative baseline 90 days after surgery
Tertiary endpoints
- Difference in total time (h) on mechanical ventilation
- Difference in mean daily dose of inotropes used
- Difference in plasma levels of interleukin-6 and C-reactive protein
- Difference in urinary levels of interleukin-18 and protein/creatinine ratio
- Difference in serum interleukin-1β and interleukin-18 concentration
- Time to first occurrence of postoperative complications, defined as low cardiac output, reoperation for bleeding, delirium, seizures, surgical site infection, sepsis, arrhythmias, cardiac arrest, pneumonia, liver dysfunction or need for blood transfusion
- Difference in total time (days) spent in the ICU
- Difference in total time (days) of index hospital stay
- Difference in rates of hospital readmission due to cardiovascular disease
- Difference in frailty evaluation, represented by the results of the Clinical Frailty Scale
- Patient reported quality of life EuroQoL-5D
Safety endpoints
- Adverse events
- Serious adverse events (i.e. adverse event that results in death, is considered life-threatening, requires or extends an hospitalization episode, causes disability or is judged as such according to the clinical criteria of the research team)
- Discontinuation of study medication due to adverse events

ICU, intensive care unit.

Adverse event data will be recorded. Serious adverse events and adverse events that lead to premature study medication discontinuation or interruption will be immediately reported. Background medication will be left to the discretion of treating physicians, in accordance with local clinical practice guidelines. Postoperative management will be performed according to each center's protocol to ensure a real-world approach.

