**Methods:**

The VERTIGO study (EudraCT: 2021-004938-11) will enroll 608 patients that require elective cardiac surgery with ECC. Patients will be randomly assigned in a 1:1 ratio to receive either empagliflozin 10 mg orally daily or placebo. Study treatment will start 5 days before surgery and will continue during the first 7 days postoperatively. All participants will receive standard care according to local practice guidelines. The primary endpoint of the study will be the proportion of patients that develop major adverse kidney events during the first 90 days after surgery, defined as ≥25% renal function decline, renal replacement therapy initiation or death. Secondary, tertiary and safety endpoints will include rates of AKI during index hospitalization, postoperative complications and observed adverse events.

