### Sample size calculation and statistical analyses

Previous studies have observed an incidence of MAKE90 of 25% among patients that required elective cardiac surgery [38, 39]. Assuming the prior proportion of MAKE90 to be 25% for the placebo group, a sample size of 546 patients (273 patients per treatment group) will provide a 90% (β = 0.10) power to detect a statistically significant difference of 10% in the proportion of patients with MAKE90 under a one-sided significance level of 5% (α = 0.05), i.e. to detect a proportion of 15% for the empagliflozin group. Finally, by taking in account a potential dropout rate of 10% we determined a sample size of 608 patients (304 patients per treatment group).

Our trial will apply adaptive Bayesian methodology to estimate the proportions of patients with the primary endpoint in both groups. For such a purpose, a conjugate beta-binomial model will be used, allowing for continuous updates of posterior distributions as new samples are obtained. This means that, as additional data are collected, proportion estimates will be dynamically adjusted, providing a real-time view of treatment effectiveness in disease prevention.

Two interim analyses will be carried out by the independent data monitoring committee. These analyses will be carried out once 30% and 60% of the planned study sample have been recruited. The objective of the first analysis will be to assess the futility of the study intervention, using conditional power analysis. The aim of the second analysis will be to evaluate the need to adjust the study sample size. Both interim analyses will be performed by an external statistician to ensure that no loss of blinding occurs.

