Primary endpoint analysis will be based on the intention-to-treat population, defined as all validly randomized patients. In the analysis of the primary endpoint, study treatments will be compared using a Cox proportional hazards regression model with a factor for the treatment group. Hazard ratio, 95% confidence interval and *P*-value will be reported. Kaplan–Meier estimates of the cumulative incidence to the occurrence of MAKE90 will be calculated. Secondary endpoints will be tested in a similar manner. If superiority is achieved for the primary endpoint, the secondary endpoints will be tested following a hierarchical order, as follows. (i) Any stage of AKI defined according to Kidney Disease: Improving Global Outcomes (KDIGO) guidelines during index admission. (ii) Stage 3 AKI according to KDIGO guidelines during index admission. (iii) Time to renal replacement therapy initiation during index admission. (iv) Time to death from any cause. Statistical significance will be required before testing the next hypothesis in the hierarchy. The effects of the planned intervention on primary and secondary outcomes will also be assessed in subanalyses stratified by sex, baseline eGFR, diabetic status and type of planned surgery (valvular/coronary/valvular and coronary).

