Several studies have observed incidence rates of MAKE90 in cardiac surgery patients of approximately 25% [38, 39]. A sample size of 608 patients will provide power of 90% to demonstrate a 10% reduction in the incidence of MAKE90 with empagliflozin versus placebo. This proportion has been chosen as it has been considered potentially achievable after reviewing the preclinical data and results of previously conducted trials on the subject, in addition to considering it as a clinically significant reduction [28, 44, 45]. Due to the existing limitations in relation to previous data, two interim analyses have been planned to evaluate futility and the need for a sample size re-estimation, applying adaptive Bayesian methodology. Results of the interim analyses will be reviewed by an independent data-monitoring committee, who will provide a recommendation to stop the trial early due to futility or to maintain or increase the sample size. All research team members, as well as participants, will remain blinded until study completion.

The primary endpoint of the study will be the incidence of MAKE during the first 90 days after surgery. This endpoint has been considered as a clinically meaningful tool that may help to increase our capacity to understand AKI in a wide variety of clinical settings, as well as providing a composite to allow comparison of potential interventions [47]. MAKE90 combines worsened renal function, defined as a decline in eGFR of ≥25%, new dialysis or death, thus including new-onset or progressive renal dysfunction of variable intensity, as well as death as the definitive major morbid outcome. A renal composite such as MAKE90 allows assessment of renal disability-free survival, securing a higher proportion of patients that suffer poor renal outcomes, in addition to eliminating potential competing risks [47].

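### The primary endpoint is a time to event in the Methods text but a proportion in Table 2, the abstract and the sample size, and the level at which it succeeds is not fixed

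*Protocol article*

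**What the plan says.** All references are to the protocol article.

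- **Outcome definitions and background medication, text:** "The primary endpoint of the study will be the time to the first occurrence of any major adverse kidney event", within 90 days of surgery.
- **Table 2, same section:** "Proportion of patients that present MAKE90, defined as one or more of the following".
- **Abstract, Methods:** "The primary endpoint of the study will be the proportion of patients that develop major adverse kidney events".
- **Discussion:** "The primary endpoint of the study will be the incidence of MAKE during the first 90 days after surgery".
- **Sample size calculation and statistical analyses, sizing:** 25% with placebo v 15% with empagliflozin, one-sided 5%, 90% power, 273 per group (546), raised to 304 per group (608) for 10% dropout.
- **Same section, Bayesian part:** "Our trial will apply adaptive Bayesian methodology to estimate the proportions of patients with the primary endpoint in both groups", by a conjugate beta-binomial model updated as data accrue. The Discussion links the Bayesian method to the two interim analyses.
- **Same section, primary analysis (intention-to-treat):** "study treatments will be compared using a Cox proportional hazards regression model with a factor for the treatment group". The output is an HR with its 95% interval and a P-value, sidedness not given. The ordered secondary tests begin only if the primary endpoint shows superiority.

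**The concern.** The text and the table of a single section give different kinds of variable as the primary endpoint, a time and a yes/no outcome. An analysis plan that is not shown cannot make both true.

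The split carries through the design. Sizing and Bayesian estimation are on the proportion scale, while the named comparison is on the hazard scale. A risk difference and a hazard ratio are different effect measures. They also treat patients lost before day 90 differently: Cox regression censors them, and a proportion has to classify them. The plan expects 10% dropout.

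The decision level is split too. The sizing is one-sided at 5%. The primary analysis reports a 95% interval, which corresponds to two-sided 5% if used as the criterion, and a P-value whose sidedness is not given. What counts as primary superiority also decides whether the secondary hierarchy opens, so any ambiguity passes on to the secondary claims.

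**Working it through.** **1. Reproduce the stated sample size.** Inputs from the sample size section: p1 = 0.25, p2 = 0.15, mean 0.20, z(0.95) = 1.645, z(0.90) = 1.2816. With pooled variance and no continuity correction:

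n = [1.645 × √(2 × 0.20 × 0.80) + 1.2816 × √(0.25 × 0.75 + 0.15 × 0.85)]² / 0.10² = [0.9305 + 0.7193]² / 0.01 = 272.2, so 273 per group (546).

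Dropout: 273 / 0.9 = 303.3, so 304 per group (608). Both figures reproduce exactly. Other variants do not give 273: two-sided 335, one-sided with continuity correction 292, one-sided unpooled 270. The sizing is therefore a one-sided comparison of two proportions.

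**2. Does the Cox scale change the size?** Assume proportional hazards.

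- Implied HR = ln(0.85) / ln(0.75) = 0.565, with ln HR = −0.571.
- Expected events = 273 × 0.25 + 273 × 0.15 = 109.2.
- Events needed at one-sided 5% and 90% power (Schoenfeld) = 4 × (1.645 + 1.2816)² / 0.571² ≈ 105.04 (using the unrounded ln HR), so 106. Freedman's formula gives 111.
- Power with 109.2 events = Φ(√109.2 / 2 × 0.571 − 1.645) = Φ(1.34) = 91%.

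At the same level, Cox has 91% power and the two-proportion test 90%.

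**3. Does the scale change the verdict?** Simulation with 273 per group, exponential event times, complete 90-day follow-up, the log-rank test as the Cox score test, and 4,000 runs per scenario. At one-sided 5%, the two verdicts differed in 0.7% of runs at 25% v 15% and in 2% at 25% v 18%.

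**4. Does the decision level matter?** Suppose success means that the 95% interval excludes the null.

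- Two proportions, 273 per group: Φ[(0.10 × √273 − 1.96 × 0.5657) / 0.5612] = Φ(0.97) = 83%.
- Cox, 109.2 events: Φ(2.984 − 1.96) = Φ(1.02) = 85%.
- Simulated log-rank: 84%.

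The one-sided 5% two-proportion rule and the rule that the 95% interval for the HR excludes 1 disagreed in about 6% of runs at 25% v 15% and 12% at 25% v 18%.

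**5. One data set, two verdicts.** Take 68/273 (24.9%) v 51/273 (18.7%).

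- Pooled proportion 119/546 = 0.218; SE = √(0.218 × 0.782 × 2/273) = 0.0353; z = 0.0623 / 0.0353 = 1.76. One-sided p = 0.039, two-sided p = 0.078.
- Under proportional hazards, HR = ln(1 − 51/273) / ln(1 − 68/273) = 0.72, with SE(ln HR) ≈ √(1/68 + 1/51) = 0.185. The 95% interval is exp(−0.326 ± 1.96 × 0.185), about 0.50 to 1.04. The 90% interval, with 1.645 in place of 1.96, is about 0.53 to 0.98.

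The trial succeeds at the level used for sizing and fails if the reported 95% interval decides. Both scales give the same answer at each level, so the conflict here is one of sidedness.

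**The case against.** The strongest reply is that the plan does name one comparison for the primary endpoint, the Cox model on the intention-to-treat population, and that it matches the time-to-event definition in the outcome text. That stands. A reader might infer that no single result decides the trial, or that three rival analyses are planned. The article supports neither. No two-proportion test is named as an analysis; proportions are the basis for sizing. The beta-binomial model is described as estimation and the Discussion ties it to the interim analyses, with no posterior success rule stated. A prior or threshold may sit in the full protocol or analysis plan, so its absence is not counted here. What remains is that the sample size section does not confine the model to the interim analyses, so its role needs a sentence.

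It is also fair to say that the choice of scale has little practical effect, as steps 2 and 3 show. That stands under proportional hazards with complete follow-up; the simulation did not include dropout.

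A reader might further argue that event times add little because eGFR is measured only at scheduled visits. The visit schedule is a figure that is not shown, and death and the start of renal replacement therapy can be dated independently of visits. That argument is not relied on.

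**Conclusion.** The plan is wrong as written on this point. Its primary endpoint has two incompatible definitions, the named Cox comparison fits only one of them, and the level at which it succeeds is not reconciled with the one-sided 5% used for sizing.

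The sample size arithmetic is correct on its own inputs and is not faulted. The effect of the scale alone is small. The effect of the level is moderate: a loss of about 5 to 7 percentage points of power at 546 evaluable patients if the 95% interval decides, with opposite verdicts possible near the boundary. These figures assume the plan's 25% and 15% rates, proportional hazards for the Cox results, and exponential event times with no dropout for the simulations.

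A reader might conclude that the risk difference must replace the Cox analysis. The documents do not require that; either version is acceptable if it is used throughout.

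**What to change.** Before unblinding, state one primary endpoint, one effect measure and one deciding analysis with its sidedness, and bring the abstract, the outcome text, Table 2, the statistical section and the Discussion into line. Two routes would do:

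- **Proportion with MAKE90 by day 90, compared as a risk difference.** This fits the abstract, Table 2 and the sizing. Reword the outcome text and make the Cox and Kaplan–Meier results supportive.
- **Time to first MAKE within 90 days, compared by the named Cox model.** Reword the abstract and Table 2, and state the sizing assumption on the hazard scale (HR 0.565, about 109 events).

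On either route, state that the interval used to judge success matches the one-sided 5% design (a two-sided 90% interval, or its one-sided 95% bound), or restate the power as about 83–85% for a 95% interval. Add one sentence that the beta-binomial model is an interim or supportive tool and does not decide the trial.

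This costs protocol and analysis-plan wording, with no extra data or patients. Only if the sponsor chose two-sided 5% and also wished to keep 90% power would the size change: to 335 per group (670 evaluable) on the proportion scale, or about 645 to 680 evaluable for Cox.

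### AKI, Stage 3 AKI and renal replacement therapy in the test hierarchy are counted over a window that closes at each patient's discharge, and the death endpoint is defined in two ways

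*Protocol article*

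**What the plan says.** Protocol article, Outcome definitions and background medication, Table 2. Four of the five secondary endpoints are limited to the index admission, with no number of days:

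- any-stage AKI: "Proportion of participants who developed any stage of AKI defined according to KDIGO guidelines during index admission"
- Stage 3 AKI: "Proportion of patients who suffered a Stage 3 AKI according to KDIGO guidelines during index admission"
- RRT: "Proportion of patients who required renal replacement therapy during index admission"
- death: "Proportion of patients who died during index admission"

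The fifth, a maintained eGFR decline, is read at 90 days. Among the tertiary endpoints is "Difference in total time (days) of index hospital stay".

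Protocol article, Sample size calculation and statistical analyses. The hierarchy keeps the admission limit for both AKI endpoints and for RRT, "iii) Time to renal replacement therapy initiation during index admission". It drops the limit for death, "iv) Time to death from any cause". Secondary endpoints are to be tested much as the primary is, which means a Cox model. The primary endpoint, MAKE90, counts eGFR decline, RRT and death to a fixed 90 days after surgery.

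Protocol article, Schedule of assessments: "Doses 7–13 will be administered daily during the first 7 days after surgery". The dosing period is thus defined in days from surgery, while the secondary endpoints are defined by discharge.

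**The concern.** Discharge happens after randomisation. By listing length of index stay as an outcome, the plan allows that treatment may change it. An endpoint counted up to discharge therefore has an observation time that can differ between arms. A patient who leaves on Day 5 can contribute five days of possible AKI; one who stays three weeks can contribute three weeks, including late AKI after sepsis or reoperation.

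The choice of analysis does not remove the difficulty. As proportions, the endpoints compare unequal windows. In a Cox model, discharge would become a censoring time, and patients are generally discharged because they are doing well, so those censored are not representative of those still at risk.

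The affected endpoints are the first three gatekept steps after the primary, so a distortion there bears on confirmatory claims. For death the issue is different: the two sections define different endpoints, and a reader cannot tell which one step (iv) reports.

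**Working it through.** **The plan's own figure.** The only computable figure is the primary sample size. With 25% v 15%, one-sided α = 0.05 and 90% power, the pooled formula gives n = [1.645·√(2·0.20·0.80) + 1.282·√(0.25·0.75 + 0.15·0.85)]² / 0.10² ≈ 272.2, so 273 per arm (546). Then 273/0.9 = 303.3, so 304 per arm (608). This agrees with the protocol. The point does not depend on it; only the 304 is used below.

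**Inputs that are not in the document.** The protocol gives no length of stay, AKI timing or late event rate. All such values below are assumptions. Each case has no drug effect and stays that differ independently of AKI.

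**AKI, closed form.** Assume a total AKI risk of 40% (the top of the protocol's background range of 20–40%) with exponential onset. If a share s of AKI has started by Day 7, then λ = −ln(1−s)/7, and the proportion counted by discharge on day L is 0.40·(1 − e^(−λL)).

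| Share by Day 7 | Stay, days | Counted AKI | Risk ratio |
|---|---|---|---|
| 99% | 7 v 8 | 39.6% v 39.8% | 0.995 |
| 99% | 6 v 8 | 39.2% v 39.8% | 0.986 |
| 95% | 7 v 8 | 38.0% v 38.7% | 0.98 |
| 95% | 6 v 8 | 36.9% v 38.7% | 0.95 |
| 80% | 6 v 8 | 29.9% v 33.6% | 0.89 |

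For the last row with 304 per arm, the mean proportion is 0.318 and the standard error about 0.038. The one-sided rejection probability is Φ[(0.0371 − 1.645·0.0378)/0.0377] = Φ(−0.66) ≈ 0.25, against a nominal 0.05. A common fixed window gives a risk ratio of 1.00 in every row.

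**AKI, simulation.** Assume an AKI hazard of 10% per day for 3 days, then 1% or 2% per day, and a stay of 4 days plus a gamma (shape 2) variable. Mean stays of 10 v 8 days give:

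- late hazard 1% per day: 30.9% v 29.5%, a gap of 1.4 points
- late hazard 2% per day: 35.3% v 32.8%, a gap of 2.5 points
- AKI to Day 7 with complete ascertainment (1% per day): 28.8% in both arms
- AKI to Day 7 when early leavers are seen only to discharge (1% per day): a gap of about 0.2 points

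**In-admission death (the Table 2 form).** With a constant hazard and 2–5% mortality at 30 days, stays of 6 v 8 days give a risk ratio of about 0.75, and 7 v 8 days about 0.875. The absolute gap is only 0.07 to 0.34 points. At 3% mortality and 6 v 8 days it is 0.61% v 0.81%, or 0.0020 × 304 ≈ 0.6 of a death per arm.

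**Scope of these figures.** They concern proportions. If discharge really were independent of risk, as assumed here, censoring at discharge would not bias a hazard ratio. The Cox problem arises because discharge depends on the patient's condition, and these models do not size that.

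**Death, side by side.** Table 2 gives a proportion, closed at discharge. The hierarchy gives a time to event, any cause, with no admission limit. A death after discharge counts in the second and not in the first.

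**The case against.** A reader might infer that an arm with shorter stays must show fewer events by construction. The documents do not support that. Bias needs stays that differ by arm and events that would have occurred after discharge, and the protocol shows neither. Listing length of stay as an endpoint does not show that the drug alters it. If the drug shortens stay because it prevents AKI, the lower count is a real effect, though a fixed window would capture that too.

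A reader might also infer that deaths after discharge are lost. They are not: step (iv) has no admission limit, and MAKE90 counts death and RRT to Day 90. Nor can one say that patients discharged early have no kidney assessment while still on study drug. The visit schedule figure is not available here, and the text says that blood and urine samples are taken at each visit.

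Other points for the plan stand. Randomisation is stratified by site, which balances centre discharge habits between arms, and double-blinding prevents discharge being steered by known allocation. KDIGO staging uses urine output, which is practical to collect mainly in hospital. Most AKI after cardiac surgery may well be early, and then little is lost. What these points do not answer is a treatment effect on stay itself, or the two definitions of death.

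**Conclusion.** The point holds in a limited form. Hierarchy steps (i) to (iii) use a counting window that ends at a post-randomisation event which treatment may affect. The comparison can therefore be distorted in either direction, depending on which arm stays longer.

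For AKI the likely size is small: a risk ratio of 0.98 to 0.995 for a one-day difference in stay if 95–99% of AKI starts by Day 7. It becomes material (0.89) only with a two-day difference and a fifth of AKI starting after Day 7. Every one of these sizes rests on assumed stays and timing. In-admission death shows larger relative distortion but well under one percentage point in absolute terms, and in a form that the hierarchy does not test.

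The inconsistency over death between Table 2 and the hierarchy needs no assumption. The primary endpoint is untouched. This is an inexpensive improvement to secondary endpoints and does not threaten the trial's main conclusion.

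**What to change.** 1. Define any-stage and Stage 3 AKI over a fixed postoperative window, for example Days 0–7, which matches the postoperative dosing period.
2. Define RRT and death through Day 90, which MAKE90 follow-up already covers.
3. Use the same definitions in Table 2 and in the hierarchy, so that death has one meaning.
4. Keep the index-admission figures as descriptive results.

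For RRT and death this is a change of wording only. For AKI there are two costs: AKI first arising after Day 7 leaves the confirmatory endpoints, and patients discharged before Day 7 are seen only to discharge unless a later creatinine exists. In the simulation model 26–44% of patients leave before Day 7, yet the capped window still reduces the spurious gap from about 1.4 to 0.2 points at the 1% per day late hazard. The change should be made before unblinding.
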